**Fig. 1: Scheme of the second study phase.**

The aim of the study is to simulate a consultation situation with transmission of an unfavorable prognosis for a very immature preterm infant. The unfavorable prognosis refers to one of the most common complications in neonatology and characteristic for very immature preterm infants - intraventricular hemorrhage with parenchymal involvement.

At the beginning of the second study section, the background is presented to the parents in an introductory video in the form of a short explanatory film (case vignette). The scenario of a premature baby with 23 5/7 weeks gestational age (GA) is described. The infant was born prematurely due to an amniotic infection syndrome. The infant subsequently experiences a complication of unilateral severe cerebral hemorrhage with parenchymal involvement on her third day of life. The participants also learn that the parents of the female preterm infant named Luisa are contacted by telephone by the attending physician for this reason. In the telephone conversation, the parents are asked to come to the ward in person for an important discussion. Following the introductory video, the study participants watch the two videos one after the other, which correspond to the cinematic implementation of a simulated, i.e. fictitious, consultation situation with transmission of an unfavorable prognosis for a premature baby in different ways.

Video A (intervention): optimistic framing

Video B (control): pessimistic framing

Prognoses can only be predicted with great uncertainty in individual cases. For this reason, the transmission of prognostic data in both scenarios refers to outcome estimation data from scientific publications.

Scripted video vignettes were identified as suitable study material for the present study. Their conception, cinematic realization, and use were in accordance with the recommendations of Hillen and van Vliet. The development and use of video vignettes was guided by the specific research question, objectives, and particular requirements of this specific research project. The conception of the scripts was inspired by a study on the influence of more or less pessimistic communication on the perception of physician compassion from and in adult oncology.

The case vignette as well as the two scripts for the two different scenarios were developed in an interdisciplinary way. The introductory video and the two videos (A and B) were shot with the support of a film team consisting of several actresses, a cameraman and camera assistance. In principle, the selected scenarios did not differ in content, but in the way the limiting prognosis was delivered (optimistic vs. pessimistic framing). The number of empathetic utterances is comparable, the different degree of optimism is achieved by variation of selected text passages. As a final thought, both scenarios contain a statement by the physician in the sense of reassurance of non-abandonment. In order to make it easier for the study participants to put themselves in the position of the parents in this consultation situation (empathization), the parents are seen from the front in the video. In the present case, a female physician communicates the prognosis. We chose a female doctor for reasons of uniformity of the videos as well as authenticity. It corresponds to the reality of most NICUs, including at the University Medical Center Mainz, that mainly women work as physicians in neonatology in this specialty.

The design of the study provides for parents included in the research project, after initial randomization, to first complete a baseline questionnaire (Data acquisition  $t_0$ , see p.22) as a later basis for possible subgroup analyses. Following each of the two consecutive videos - regardless of the order in which they are presented - the subjects answer questions in the form of a post-intervention questionnaire (see Data acquisition  $t_1 + t_2 + t_{end}$ , p. 23ff).

## 2. Endpoints of the study

### Primary endpoint

1. Parental preference for pessimistic versus optimistic message framing:
  - a. Patient parents' preference for video B or A (dichotomous question with 1 = first video and 2 = second video).
  - b. Rating of the desired level of optimism when an unfavorable prognosis is conveyed (unimodal, fully verbalized 7-point rating scale ranging from 1 = not at all optimistic to 7 = very optimistic).

### Secondary endpoints

1. State anxiety is assessed using the German short version (5 items) of the State-Trait Anxiety Inventory (STAI-SKD) scale. is used to assess state anxiety. Here, the change in parental (state) anxiety by/after viewing the first video is determined as the difference in state anxiety at time points  $t_0$  and  $t_1$ .
2. Parental satisfaction is assessed using a fully verbalized 7-point rating scale (unimodal with 1 = not at all satisfied to 7 = very satisfied).
3. The realism of the parental assessment of the prognosis is determined by the degree of agreement between subjective assessment and objective ability to reproduce the transmitted prognostic data:
  - a. Subjective assessment of the severity of the prognosis is based on a statement to be rated by the parents using a fully verbalized 7-point rating scale (1 = very bad to 7 = not bad at all).
  - b. The objective ability to reproduce the transmitted information is based on the recall of the outcome data in numerical values (relative probabilities in %).
  - c. The degree of parental preparedness for timely treatment decision-making is assessed using a fully verbalized 7-point rating scale (1 = not at all prepared to 7 = completely prepared).

*Note: At the end of the study, parents are also asked to provide a general assessment regarding the importance of physician-parent interviews as well as the transmission of prognoses (i.e., probabilistic data) in particular (see Data acquisition  $t_{end}$  on p. 24).*

4. The degree of parental optimism with regard to the child's future is determined by evaluating two statements (a) on survival of the complication per se and (b) on survival without impairment via the

respective fully verbalized 7-point rating scale (unimodal with 1= not optimistic at all to 7 = very optimistic). It is taken into account in the evaluation that the degree of optimism may depend on the participants' basic attitude towards life. The basic attitude towards life is therefore initially measured using the scale Optimism-Pessimism-2 (SOP-2). recorded.

5. The degree of perceived hopefulness is assessed using a fully verbalized 7-point rating scale (unimodal with 1= not at all hopeful to 7 = very hopeful). A possible correlation of the individual expression of parental hope recorded in the baseline using the German version of the Herth-Hope Index (HHI-D) with the assessment of parental hope (lack of hope) following the video.
6. Parents rate on a fully verbalized 7-point rating scale how prepared they felt by the interview to make a treatment decision with the clinician in a timely manner (1 = not at all prepared and 7 = completely prepared).
7. The general impression of the consulting physician on the parents is determined using a fully verbalized 5-point rating scale (German school grades 1 to 5)
8. To assess physician professionalism, the German translation of a subscale of the Professional Performance Questionnaire adapted from  (verbal anchoring with German school grades 1 to 5; sum score: range 9 - 45 points) is used. A back-translation by a native speaker was performed.
9. Physician compassion was assessed with the help of the German-translated version of the Physician Compassion Questionnaire according to  (5 items, polarity profiles with 10 scale points each; sum score: range 5-50). A back-translation by a native speaker was performed.

Additionally for physicians:

10. In this case, the evaluation of a colleague questionnaire is used to assess the *colleague* advising in the video. .
11. A fully verbalized rating scale (range 1-7) is used to self-assess the individual approach of the participating physician.

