### **2.2 Secondary research questions - secondary hypotheses**

1. With pessimistic framing, parental (state) anxiety is greater than with optimistic framing.
2. With pessimistic framing, parental satisfaction with communication is greater than with optimistic framing.
3. With pessimistic framing, parents estimate the conveyed outcomes more realistically than with optimistic framing.
  - a. With pessimistic framing, parents show less deviation in the recall from the communicated relative probabilities (probabilistic data) regarding survival of the preterm infant (general or without impairment).
  - b. With pessimistic framing, parents report a higher severity of the child's expected impairment.
  - c. With pessimistic framing, parents report a higher degree of being informed regarding the prognosis.
4. With pessimistic framing, parents are less optimistic about the patient's future than with optimistic framing.
  - a. With pessimistic framing, parents are less optimistic that the patient will survive the cerebral hemorrhage.
  - b. With pessimistic framing, parents are less optimistic that the patient will survive without (cognitive/physical) impairment.
5. With pessimistic framing, parents express less hopefulness about the patient's future.
6. With pessimistic framing, parents indicate a higher degree of preparation to make a treatment decision together with the attending physician.
7. With pessimistic framing, the physician makes a better general impression on parents.
8. With pessimistic framing, parents rate the physician as more professional.
9. With pessimistic framing, parents rate the physician as less compassionate.
10. Physicians prefer pessimistic framing to an optimistic framing.
11. Physicians estimate the severity of prognosis more objectively when prognosis is framed pessimistically than when prognosis is framed optimistically.

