**Data acquisition  $t_1$  after the first video (A or B)**

Parents are asked to rate the degree of optimism of prognosis communication on a 7 point rating scale (1 = not at all optimistic to 7 = very optimistic).

- Parents' (state) anxiety is assessed using the German short version (5 items) of the State-Trait Anxiety Inventory (STAI-SKD) scale..
- Parental satisfaction with the way the clinician communicated the prognosis is assessed using a fully verbalized rating scale (range 1-7).
- The realism of parental assessment of prognosis is determined by the correlation between subjective assessment of the severity of prognosis (fully verbalized rating scale, range 1-7) and objective ability to reproduce the prognostic data conveyed. It will solicit a selection from percentages ranging from 0 to 100 percent in increments of ten (survival) or twenty-five (impairment).
- Parental level of optimism about the child's future (overall survival and survival without impairment) is assessed using a fully verbalized rating scale (range 1-7).
- A fully verbalized rating scale (range 1-7) is used to assess the degree of perceived hope (hopelessness).
- Using a fully verbalized rating scale (range 1-7), parents are asked whether they felt prepared to make a joint (treatment) decision with the physician in the announced follow-up interview.
- The general impression of the consulting physician on the parents is visualized by a fully verbalized rating scale (school grades 1 to 5, equal to the scale of the Professional Performance Questionnaire adapted to , sum score: 5-50) visualized.
- Physician professionalism is assessed using the German translation of a subscale of the Professional Performance Questionnaire (school grades 1 to 5, sum score: range 9 - 45 points) adapted from  determined.
- Physician compassion is assessed using the German translation of the Physician Compassion Questionnaire in a slightly modified version adapted from in a slightly modified version. The labels of the poles of the 5 items depicting the five dimensions of physician compassion were translated literally and back-translated by a native speaker, the scaling corresponds to a numerical rating scale with range 1-10.

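### Secondary endpoint 3 defines realism as agreement or correlation between a severity rating and recall, which does not match hypothesis 3a on deviation from the communicated probabilities

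*Protocol*

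**What the plan says.** Protocol section II.2.2 gives hypothesis 3: "With pessimistic framing, parents estimate the conveyed outcomes more realistically than with optimistic framing". Part 3a makes this concrete: "parents show less deviation in the recall from the communicated relative probabilities (probabilistic data) regarding survival of the preterm infant", either overall or without impairment.

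Section III.2, secondary endpoint 3, turns the hypothesis into a measure: "The realism of the parental assessment of the prognosis is determined by the degree of agreement between subjective assessment and objective ability to reproduce". What has to be reproduced is the set of outcome figures given in the video. The first component of the measure is a severity rating on a "fully verbalized 7-point rating scale (1 = very bad to 7 = not bad at all"). Its second is recall of the outcome figures as percentages.

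Section V.2, data acquisition at t1, restates the measure: "The realism of parental assessment of prognosis is determined by the correlation between subjective assessment of the severity of prognosis" and the ability to reproduce the prognostic data. Recall is chosen from "percentages ranging from 0 to 100 percent in increments of ten (survival) or twenty-five (impairment").

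Neither III.2 nor V.2 defines a difference between the recalled and the communicated percentage.

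**The concern.** Hypothesis 3a is about accuracy: how far each parent's recalled figure lies from a known value, and whether that distance differs between framings. The endpoint describes something nearer to internal consistency, namely whether parents who recall better figures also rate the prognosis as less bad. A parent who recalls far too high a survival figure and rates the prognosis accordingly is fully consistent and quite unrealistic.

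The answer to hypothesis 3 is at stake. An analyst who follows III.2 and V.2 literally could rank the two framings in the wrong order. An analyst who sees the problem would have to choose among agreement, correlation and deviation after the data are in.

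**Working it through.** **The plan's own figures.** None is stated for this endpoint. The sample sizes in VI.1 concern the primary endpoint only. They reproduce with a two-sided 5% test of two proportions at 80% power: 0.4 vs 0.6 gives 97 per sequence, so 194; 0.50 vs 0.3077 gives 102 per sequence, so 204; and 204 / 0.95 = 214.7, so 215. Nothing below changes them.

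**Agreement.** Agreement needs two measurements on one scale. A verbal rating from 1 to 7 and a percentage have no common unit, and the protocol gives no mapping between them.

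**Correlation: what follows without any assumed number.** Let R be the recalled percentage, S the severity rating and c the communicated percentage, which is constant within a first-video group.

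1. If all recalls in a group shift by a constant b, Cov(R + b, S) = Cov(R, S) and the variances are unchanged. The correlation does not move, however large the bias.
2. If ability to reproduce is read as signed error R − c, then corr(R − c, S) = corr(R, S), because c is constant. The result is the same.
3. If it is read as absolute error |R − c|, doubling every parent's error leaves the correlation with S unchanged. It still does not say which group errs less.
4. If every parent recalls c exactly, R, R − c and |R − c| have no variance and the correlation is undefined.
5. The correlation is one number per group, so it supplies no per-parent score of the kind that 3a describes.

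**Illustration.** The assumptions are: latent recall normal around c; recall rounded to 10-point steps, as in V.2 for survival, and limited to 0–100; rating = 1 + 6 × (latent value without bias + noise with SD 8) / 100, rounded and limited to 1–7; Spearman correlation; 200,000 draws per setting. The protocol does not give c, so 30, 50, 60 and 70% were tried.

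*Constant bias, c = 60%, latent SD 12:*

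| Recall bias (points) | Mean absolute error (points) | Correlation |
|---|---|---|
| 0 | 9.3 | 0.75 |
| 10 | 12.5 | 0.75 |
| 20 | 20.2 | 0.75 |
| 30 | 28.8 | 0.74 |

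At c = 30% and 50% the correlation stays at 0.75 to 0.76 while the error rises from about 9 to about 30 points. At c = 70% the ceiling at 100% lowers the correlation to 0.64 at the largest bias, where the error is 25.4 points.

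*No bias, c = 60%, spread varied:*

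| Latent SD (points) | Mean absolute error (points) | Correlation |
|---|---|---|
| 3 | 0.9 | 0.19 |
| 6 | 4.2 | 0.48 |
| 12 | 9.3 | 0.75 |
| 20 | 15.6 | 0.89 |

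The reason for the second table shows before rounding. With latent SD s and noise SD 8 the correlation is s / √(s² + 64): 3/√73 = 0.35, 6/√100 = 0.60, 12/√208 = 0.83, 20/√464 = 0.93. Rounding lowers these values but keeps their order. The more tightly parents cluster on the right answer, the lower the correlation, so a group with larger errors can look more realistic.

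**The case against.** Much of the case on the other side stands, and it limits the point.

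- **A reader might infer that hypothesis 3a cannot be tested.** The protocol does not support that. Recalled percentages are collected as a separate component, and 3a states its own comparison, so a deviation score follows by subtraction. Nothing says that only the combined measure will be reported.
- **A reader might infer that the communicated value plays no part in the measure.** That depends on how ability to reproduce is read, since it may mean recall judged against what was transmitted. On that reading the value enters, but steps 2 and 3 of the working show that the correlation still does not rank the framings by accuracy. The simulation uses raw recall; by step 2 its correlations also hold for signed error.
- **A reader might quote a sharper contrast**, such as a correlation of 0.00 with a mean error of 4.2 points against 0.49 with 22.7 points. Those figures assume that recall is unrelated to severity in the accurate group and tied to it in the biased group, so part of the gap is built in. With the same link in all groups, the setting with an error of 4.2 points gives 0.48. A reversal is possible under chosen inputs; it is not predicted.
- **A reader might fault the 25-point response steps for impairment.** The communicated impairment figure is not in the protocol. If it lies on the grid the forced error is zero; otherwise it is at most 12.5 points. A value of 25% or 75% would fit the present grid and not a 10-point one. No fault is shown, and no change of grid can be recommended.
- **The text is a translation**, so the difference between agreement and correlation should not be pressed. Neither word fits 3a.
- **Scoring is often left to the analysis plan.** Here, though, the protocol states a definition twice, and it departs from the protocol's own hypothesis. That is more than an omitted detail.

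**Conclusion.** The point holds as a mismatch between an endpoint definition and its hypothesis. Endpoint 3 in III.2 and the t1 text in V.2 define realism as agreement or correlation between a severity rating and recall; hypothesis 3a concerns deviation of recalled from communicated probabilities. Agreement across unlike scales is undefined. A correlation is blind to constant bias, can fall as recall improves, and is undefined under perfect recall, so the stated rule could favour the framing with worse recall.

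The bias and zero-variance arguments need no assumed values. The sizes in the tables do: they rest on assumed communicated percentages, spreads and rating noise, and only illustrate what can happen. The fault lies in the definition and not in the data collected. One secondary endpoint is affected; the primary analysis and the sample size are untouched. The definition should be corrected before the data are analysed.

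**What to change.** In III.2 item 3 and in V.2 (data acquisition at t1):

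- Define the 3a endpoint per parent as the absolute difference between recalled and communicated percentage, with the signed difference alongside to show the direction of bias, separately for survival and impairment.
- Compare it between the two first-video groups at t1, allowing for two parents from one family as the primary analysis already does.
- Report the severity rating as an outcome in its own right.
- Keep any correlation between rating and recall as descriptive only.

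The cost is a few sentences of rewording. No item, response scale, visit or participant is added, and the sample size does not change.

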## IV. Study participants

### 1. Complete inclusion criteria

- Parents of former premature infants (birth weight < 1500 g and born after 31.12.2009)
- Postnatal treatment of a premature infant at University Medical Center of the Johannes-Gutenberg University Mainz
- Physicians with at least 6 months of work experience in a NICU.

Explanation: There will be two separate sub-projects. One study with parents as participants and one with physicians.

The study is to be carried out with the inclusion of the selected parents as well as medical personnel who are confronted with such complex scenarios in their daily work. It must be assumed that the special circumstances of the experience of a situation comparable to the scenario by parents in the past plays an important role in the influence of more or less optimistic framing of an unfavorable prognosis, for example, on the assessment of medical personnel as well as the preference of a certain type of prognosis transmission to be investigated. The expertise of the selected parental study collective is thus a prerequisite for gaining knowledge in the context of this survey. This study deliberately refrains from including parents who are actually acutely confronted with the situation of a serious complication of their preterm infant.

### 2. Complete exclusion criteria

- Lack of informed consent
- Insufficient knowledge of German language
- Self-reported acute, severe mental illness

### 3. Are subjects included who have doubts about their ability to consent or who do not have the ability to consent?

No

### 4. Will subjects lacking capacity to consent be included in the research project?

No.

### 5. How are subjects recruited and is recruitment material used?

Patient parents will be recruited in person, i.e. by mail, telephone, and electronically or in the course of a medical consultation, e.g. at discharge or in the course of the developmental neurological follow-up for former preterm infants at Mainz University Medical Center, as well as by contacting and via the parents' association of preterm infants "Frühstart e.V.". If parents are interested in participating, they successively contact the study team in person or electronically. (Assistant) Physicians with at least 6 months of work experience will be recruited in person and electronically.

## V. Study procedures

### 1. Approach to participants

The recruitment of suitable study participants is carried out by the initially listed study personnel. The associated verification of compliance with the predefined inclusion and exclusion criteria serves to ensure the recruitment of suitable parents for the study.

Following the acquisition (by post and personal telephone conversation), the information sheet, the consent form and the data protection information on the study are handed out to the test subjects electronically (e-mail). Accordingly, after receipt of the e-mail and before the start of the study, the parents can take sufficient time (at least 24 hours) to consent to or decline participation in the study. The second phase of the research project and thus participation in the study does not begin until the consent form is signed electronically. Participation can be withdrawn verbally or in writing before or at the beginning and at any time without giving reasons. Non-participation or early withdrawal from the study will not result in any disadvantages for the subjects. The same procedure for inclusion in the research project applies to female physicians.

